# Objectives

The primary aim of this study among patients aged ≥ 65 years admitted with an acute illness to an internal medicine unit of a community hospital in north western Switzerland is:

1. To assess the efficacy and safety of a simple prescriber checklist for reducing inappropriate prescribing and polypharmacy.

Secondary aims are:

1. To assess the number of prescribed drugs, the prevalence of polypharmacy (concomitant use of ≥ 5 drugs) and hyperpolypharmacy (concomitant use of ≥ 10 drugs).
2. To assess the prevalence of potentially inappropriate medicine use (PIMs; according to STOPP criteria) and of potentially inappropriate prescribing omissions (PPOs; according to START criteria).
3. To assess the prevalence of prescription and the rate of inappropriate prescription of following drugs: non-steroidal anti-inflammatory drugs (NSAID); proton pump inhibitors (PPI); systemic corticosteroids; metamizol-natrium (Novalgin™); potent opiates.

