The medical team on the wards will integrate the use of the described checklist in usual care of all patients hospitalised in the Department of Internal Medicine. The checklist is a tool to improve the application of strategies which are considered standard of care to optimize drug prescriptions and avoid errors or adverse drug events (Scott IA, 2012; Dovjak P, 2012; Meyer-Nikolic VA, 2012).

1. ***Follow-up***

As safety parameter we will assess the all-cause re-hospitalisation rate at 30 days after discharge using administrative data of the hospital. We believe that the re-admission rate calculated only on the basis of re-hospitalisations at the Kantonsspital Olten is representative because the Kantonsspital Olten is the only hospital in the eastern part of the Canton Solothurn and the great majority of patients discharged from the internal medicine unit of the Kantonsspital Olten come back at the same hospital if any new or recurrent problem occur after discharge.

1. ***Data collection***

At the Department of Internal Medicine, Kantonsspital Olten, most patient information (including diagnoses, therapy at admission and discharge, laboratory results, progress notes, etc.) is currently recorded in the electronic patient record. However, some other information, such as one part of the nursing documentation, is still on paper. Data will be collected from the electronic patient records and completed, if necessary, by review of the paper patient records. The medication at admission and discharge of each patient will be reviewed independently by two of the investigators ([name], [name]), who will assess whether the medication is appropriate or inappropriate according to STOPP and START criteria. Discrepancies in this assessment will be resolved by consensus. Following data will be recorded on a standardised case report form: age; gender; place of residence (home or nursing home); number of diagnoses; Charlson Comorbidity Index (Charlson ME, 1987); length of stay; number of medications at admission and discharge; prescription of NSAID, PPI, systemic corticosteroids, metamizol-natrium, potent opiates, at admission and discharge, and whether these prescriptions are appropriate or not; number of potentially inappropriate medicines (PIM) used and number of potentially inappropriate prescribing omissions (PPO), both at admission and discharge; all-cause re-hospitalisation at 30 days.

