Only the investigators will have access to the case report forms, which will be stored in a locked cabinet in the office of the investigators at the Kantonsspital Olten. For statistical analysis data will be anonymised.

1. ***Outcomes***

The primary outcome is the reduction of the proportion of patients using inappropriate drugs (PIM) at discharge and the reduction of the number of prescribed medications at discharge.

Secondary outcomes are:

1. the proportion of patients with potentially inappropriate prescribing omissions (PPOs) at admission and discharge,
2. the prevalence of prescription and the rate of inappropriate prescription of following drugs: non-steroidal anti-inflammatory drugs (NSAID); proton pump inhibitors (PPI); systemic corticosteroids; metamizol-natrium (Novalgin™); potent opiates at admission and discharge,
3. the all-cause rehospitalisation rate at 30 days after discharge

in the intervention and in the control group.

1. ***Sample size***

The sample size is determined by the estimated change in the proportion of users of inappropriate drugs at discharge and the expected size of the intervention effect. Given the high prevalence of polypharmacy in elderly patients (58% in Europe according to Gallagher et al., Gallagher P, 2011) and that 34-77% of these patients use at least one inappropriate drug (PIM), we believe that even a reduction of 10% in patients taking inappropriate medications or a reduction of 10% in the prevalence of polypharmacy will be of clinical relevance. To detect an effect of 10% of the checklist (decrease in prevalence of inappropriate drug prescription and/or polypharmacy from 30% at admission to 20% at discharge) with a probability (power) of 90% at a significance level of 0.05, a sample size of 824 patients (412 in each group) will be needed (table 1.). Therefore, we aim to include 900 patients (450 patients in the intervention group enrolled during the period September-November 2013, and 450 patients in the control group who had been hospitalised in September-November 2012).

1. ***Statistical methods***

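### Under-treatment is judged only by the proportion of patients with any START omission, although the number of omissions is recorded at admission and discharge and would show the change within each patient

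*Protocol*

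**What the plan says.** Protocol, Objectives, states the primary aim: "To assess the efficacy and safety of a simple prescriber checklist for reducing inappropriate prescribing and polypharmacy". Safety is therefore not an afterthought.

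Protocol, Outcomes, gives the primary outcome two parts: "the reduction of the proportion of patients using inappropriate drugs (PIM) at discharge" and "the reduction of the number of prescribed medications at discharge". The second part counts all drugs and does not separate indicated from inappropriate ones. The first secondary outcome is "the proportion of patients with potentially inappropriate prescribing omissions (PPOs) at admission and discharge", compared between the 2013 and 2012 cohorts. The secondary aims likewise speak of the prevalence of omissions.

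Protocol, Data collection, goes further than the outcome list. The case report form takes the "number of potentially inappropriate prescribing omissions (PPO), both at admission and discharge". Two investigators apply the STOPP and START criteria to each patient's medication at both times.

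Protocol, Follow-up, names one safety measure: "As safety parameter we will assess the all-cause re-hospitalisation rate at 30 days after discharge using administrative data of the hospital".

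Protocol, Statistical methods, compares the cohorts at admission and at discharge with chi-squared or Fisher tests for categorical variables and the Mann-Whitney test for continuous ones.

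**The concern.** A checklist aimed chiefly at polypharmacy can lower the drug count by removing drugs that should not be taken or drugs that should. The drug-count outcome cannot tell the two apart, so another outcome has to. The omission outcome is the only specific candidate, and its definition makes it a weak one, for three reasons:

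- **Masking.** A patient with one omission on admission and three at discharge is scored the same at both times.
- **Cancelling.** One patient whose omission is corrected offsets one patient in whom an omission is created.
- **Admission status ignored.** Discharge prevalence is compared between cohorts without using what each patient had on admission. Most of what is present at discharge may have been there on arrival. In a non-randomised before-after design, a difference between cohorts at admission also carries through to discharge.

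At stake is the safety half of the primary aim. A flat omission prevalence next to a lower drug count could be taken as reassurance that it does not give.

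**Working it through.** **The protocol's own figure.** The sample size concerns 30% versus 20%, not omissions. With two-sided alpha 0.05 and 90% power, the uncorrected size is [1.96·√(2·0.25·0.75) + 1.2816·√(0.21 + 0.16)]² / 0.10² = 392 per group. The continuity correction, (n/4)·[1 + √(1 + 4/(n·0.10))]², raises it to 412, the stated number. It says nothing about power for omissions. Only the planned 450 per group is carried forward.

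**Assumptions (none is in the protocol).** A share p of patients has at least one PPO on admission, with p = 30%, 45% or 60%. New omissions arise in r = 5% of control and 10% of checklist patients, independently of existing ones. At first no omission is corrected.

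**Formulas.** Discharge prevalence = p + (1 − p)·r. Power = Φ[(d − 1.96·s0)/s1], where d is the difference, s0 = √(2·p̄(1 − p̄)/n) and s1 = √{[p1(1 − p1) + p2(1 − p2)]/n}.

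**Worked case, p = 30%.** Prevalence is 0.30 + 0.70·0.05 = 33.5% versus 0.30 + 0.70·0.10 = 37.0%, so d = 0.035. With n = 450, s0 = 0.03185 and s1 = 0.03183. Power = Φ[(0.035 − 0.0624)/0.0318] = Φ(−0.86) = 19%.

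**Proportion with a new PPO, 5% versus 10%, n = 450.** s0 = 0.01756 and s1 = 0.01748. Power = Φ[(0.05 − 0.0344)/0.0175] = Φ(0.89) = 81%, whatever p is.

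**Same yes/no outcome, only in patients free of PPO on admission.** The rates are again 5% versus 10%, with n = 450·(1 − p) per group.

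| p | Discharge prevalence | Difference (points) | Power, discharge prevalence | PPO-free per group | Power, PPO-free only | Power, new PPO |
|---|---|---|---|---|---|---|
| 30% | 33.5 v 37.0% | 3.5 | 19% | 315 | 66% | 81% |
| 45% | 47.75 v 50.5% | 2.75 | 13% | 248 | 56% | 81% |
| 60% | 62 v 64% | 2.0 | 9% | 180 | 44% | 81% |

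**Splitting the gap.** Going from discharge prevalence to the PPO-free analysis measures the cost of ignoring admission status: 66 − 19 = 47, 56 − 13 = 43 and 44 − 9 = 35 points. Going from there to the new-PPO outcome measures masking: 81 − 66 = 15, 81 − 56 = 25 and, from unrounded values, 38 points. Ignoring admission status is the larger part at 30% and 45%. At 60% the two are about equal.

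**Adding corrections.** With Poisson admission counts and 10% of PPO patients having an omission corrected in each cohort, simulation gives these powers at p = 30%, 45% and 60%:

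- discharge prevalence: about 20%, 14% and 10%;
- number of PPOs at discharge alone: about 21%, 16% and 11%;
- change in number, discharge minus admission: about 67%, 63% and 56%.

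The gain therefore comes from using each patient's own admission value. Replacing a yes/no by a count at discharge adds little.

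**The case against.** The strongest reply is that nothing is lost. The count is on the case report form at both times, so a patient who goes from one omission to three is in the data. Summaries of a collected variable, and any conditioning on admission status, could be left to a statistical analysis plan. START was included to balance the focus on reducing drugs, and 30-day rehospitalisation is a named safety measure. The rates above are all assumed, and a new-PPO outcome has its own blind spot because it ignores corrected omissions.

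Much of this stands, and it rules out some stronger readings that a reader might infer:

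- *New omissions are not measured.* They are counted; they are missing only from the outcome list.
- *Every stopped drug is scored as a primary success.* That applies to the drug-count part alone, and even there a started drug offsets a stopped one. The PIM part improves only when a patient has no PIM left.
- *No other outcome could detect the harm.* Rehospitalisation could, but it is all-cause, limited to 30 days and one hospital's records, and cannot show that an indicated drug was stopped.
- *The whole gap of 81% against 19% to 9% is due to the yes/no coding.* Masking explains 15 to 38 points of it.

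The reply does not remove the point that the protocol itself fixes the outcome, as a prevalence at two separate times. That definition is explicit, not a detail left open. The blind spot of the new-PPO outcome is a reason to pair it with the net change.

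**Conclusion.** The point holds as a weakness in how an outcome is defined. Masking, cancelling and the disregard of admission status follow from the definition and need no assumed rates. A flat PPO prevalence therefore cannot by itself support a statement that under-treatment did not increase.

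The size is illustrative. It rests on an assumed 30-60% PPO prevalence at admission, new omissions in 5% versus 10%, independence and 450 per group. Within that range, discharge prevalence has about 9% to 19% power. Change in count has about 56% to 67% when some omissions are corrected, and the new-PPO proportion about 81%. Other rates would give other figures.

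The documents do not show that the checklist leads to the stopping of indicated drugs, or that this is its most likely harm. That is a plausible judgement from its focus on polypharmacy. Nor do they say that a flat prevalence will be reported as evidence of safety. The primary analysis and the sample size are unaffected.

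**What to change.** In Follow-up and Outcomes, name PPO as a safety outcome alongside 30-day rehospitalisation, and compare between the 2012 and 2013 cohorts:

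1. the per-patient change in the number of PPOs, discharge minus admission;
2. the proportion of patients with at least one PPO at discharge that was absent on admission.

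Report corrected omissions next to new ones. Keep the prevalence at each time as a descriptive figure, and state that no conclusion of unchanged under-treatment will be drawn from it alone.

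The first comparison uses numbers already on the case report form. The second needs the two investigators who already apply START to mark which discharge omissions are new, since the net change cannot show this when one omission is corrected and another created. The cost is wording, a little coding and one or two more secondary comparisons.
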